#### Energy and Macronutrient Intake

The amount of kilocalories consumed as well as saturated fat, trans fat, sodium, and added sugar will be measured.

### Statistical Analysis

Descriptive statistics will be used to characterize variables, and tables will be made with summary measures. Independent *t* tests and chi-square tests for categorical data will be used to compare baseline characteristics between the intervention and control groups. The Mann-Whitney *U* test will be used to evaluate differences between groups in case of nonnormal distribution.

Repeated measures ANOVA will be used to evaluate the change in the number of warning labels in nutrient consumption between groups and throughout the intervention. We will use a mixed-effects model to evaluate the effect of the intervention on changes in food and beverage selection, adjusting for confounding variables. Intention-to-treat analysis will be performed.

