## Methods

### Recruitment and Study Design

Third-, fourth-, and fifth-grade elementary school students and their caregivers from 4 primary schools—2 public and 2 private schools—in Mexico City will participate in the study. The schools will be chosen by simple random sampling. Schools will be randomized into 2 groups: intervention and control.

After approval from the directors of the primary schools, meetings will be held with parents to invite them to participate; they will be explained the intervention’s objectives, activities, and duration. Parents and schoolchildren will be invited to sign a consent and informed assent, respectively, clarifying that their participation is voluntary, and they may choose to discontinue at any time without affecting their activities at school.

The main question this study aims to answer is the following: What is the effect of a digital educational intervention about front-of-package warning labels on food selection among children attending primary schools in Mexico City, compared to a control group?

Schools will be randomized into 2 groups. In the control group, the dyads (caregiver-schoolchildren), will receive general nutritional education, and in the intervention group, they will also receive guidance on reading labels, which raises awareness about the impact of consuming processed or ultraprocessed foods on health.

The intervention will be carried out via a website [23] (Figure 1) with audiovisual material, and all participants will also be asked to complete a multiple-choice evaluation (5 questions) to ensure a theoretical understanding of the topics. Other measures will include a lunch register, 24-hour dietary recall, a survey of food habits and consumption, a validated food preference questionnaire, anthropometric measurements (eg, weight, height, and waist circumference), a socioeconomic survey, as well as participation in a simulated web-based food and beverage selection and shopping activity. These measures will help assess if the digital educational intervention on front-of-package warning labeling for children and caregivers improves the selection and purchase of foods.

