### Primary Outcomes

#### Time Frame

The measurements will be carried out in 2 scenarios (in schools and through the website) at baseline (1 week before starting the educational interventions), at 3 months, and at 6 months after the intervention ends.

A socioeconomic survey will be used in the baseline measurement.

The following assessments will be conducted at 3 frame times (baseline, 3 months, and 6 months): a food preference questionnaire, a 24-hour dietary recall, lunch register, and a survey of food habits and consumption. Anthropometric measurements (eg, weight, height, and waist circumference) will only be performed at baseline and the end of the 6-month intervention.

Through the website, dyads will engage in food and beverage purchasing exercises in the online shop simulator at the 3 measurement points (baseline, 3 months, and 6 months), along with multiple-choice evaluation (5 questions).

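### Without imputation, the repeated-measures ANOVA of warning labels in nutrient consumption would leave out any child with a missed visit, which fits poorly with intention to treat

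*Protocol article*

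**What the plan says.** The Statistical Analysis section of the protocol article assigns two longitudinal methods to two differently named outcomes.

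- For the label count, the sentence opens "Repeated measures ANOVA will be used to evaluate the change" and reads in full: "Repeated measures ANOVA will be used to evaluate the change in the number of warning labels in nutrient consumption between groups and throughout the intervention".
- For the shop outcome: "We will use a mixed-effects model to evaluate the effect of the intervention on changes in food and beverage selection, adjusting for confounding variables".

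The section closes with: "Intention-to-treat analysis will be performed". It does not define that population, does not say how a missed visit is handled, and does not say that the ANOVA is restricted to children with complete data.

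Under Time Frame, the dietary and preference instruments follow a three-point schedule: "The following assessments will be conducted at 3 frame times (baseline, 3 months, and 6 months". The online shop exercise follows the same three points. Under Recruitment and Study Design, families are told that "they may choose to discontinue at any time without affecting their activities at school", so incomplete series are foreseeable. That section also gives the main question: "What is the effect of a digital educational intervention about front-of-package warning labels on food selection among children".

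**The concern.** Classical repeated-measures ANOVA works on one complete row per child. With three visits and no imputation, a child seen at baseline and 6 months but absent at 3 months contributes nothing, and neither does a child seen at baseline and 3 months who then leaves. What remains is an analysis of completers. Intention to treat is meant to keep everyone in the comparison under the allocated arm, so the named method and the named principle pull in different directions for this outcome.

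Two things are at stake. Observed data are thrown away, which costs precision. And if the children who complete all visits differ between arms, the comparison is no longer between the groups that randomisation formed. The next sentence of the same section already names a method that uses partial series, so the restriction is avoidable.

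**Working it through.** The article gives no sample size, dropout rate or power figure, so there is no stated figure to reproduce. The size below rests on assumed missingness.

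**Inputs from the article**
- Three measurement points: baseline, 3 months, 6 months (Time Frame).
- Repeated-measures ANOVA for the label count, mixed-effects model for food and beverage selection (Statistical Analysis).
- Participants may leave at any time (Recruitment and Study Design).

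**Assumptions**
- Baseline is complete.
- A share q of children misses each follow-up visit, with q = 10, 15 or 20%.
- Nothing is imputed.

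**Share of children lost to the ANOVA**
- Same children miss both follow-ups: loss = q.
- Absences at 3 and 6 months independent: loss = 1 − (1 − q)².
- Lost children who nevertheless have a 6-month value, under independence: q(1 − q). If the same children miss both visits, this is 0.

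| q | Loss, same children | Loss, independent | Of which 6-month value observed (independent) |
|---|---|---|---|
| 10% | 10% | 1 − 0.90² = 19.0% | 0.10 × 0.90 = 9.0% |
| 15% | 15% | 1 − 0.85² = 27.75% (28%) | 0.15 × 0.85 = 12.75% |
| 20% | 20% | 1 − 0.80² = 36.0% | 0.20 × 0.80 = 16.0% |

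The last column is the clearest waste: children measured at both ends of the study but excluded for a missed middle visit. When the same children miss both follow-ups, the excluded children have only a baseline value, so the ANOVA discards little that bears on change.

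**Illustration by simulation** (400 children and 10% independent missingness per follow-up visit, both assumed). Complete-case analysis kept 321 of 400 children, a loss of 79/400 = 19.75%, close to the 19% from the formula. A random-intercept mixed model on the same data used all 400 children and 1113 observations. The complete cases supply 321 × 3 = 963 of these, so complete-case analysis set aside 1113 − 963 = 150 observed values.

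With no missing visits, or with imputation, the ANOVA loses no child.

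**The case against.** The strongest reply is that the article contains no contradiction. A reader might infer one from the ANOVA and intention to treat standing in the same section, but the text never says the ANOVA is limited to complete cases. Intention to treat can be read as analysis by allocated arm, and a repeated-measures ANOVA on imputed data would satisfy it. Handling of missing data is commonly left to an analysis plan or full protocol that is not shown, so its absence here is not an error. All of this stands. What is left is a point about the choice of method: the ANOVA needs imputation to be rescued, whereas the mixed model already planned uses partial series as they are.

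Other tempting extensions are also not supported:

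- *The main question is compromised.* It is not. It concerns food selection, which is assigned to the mixed-effects model.
- *Two methods allow a choice between conflicting results.* As written, each method belongs to a differently named outcome. The label-count outcome is loosely worded, but the article does not offer two analyses of the same one.
- *Less motivated families drift away from the website and so bias this ANOVA.* Time Frame ties the website to the shop exercise and the multiple-choice test and lists the dietary instruments separately. Loss of website users would bear mainly on the shop outcome. Differential loss for the label count is possible but not shown.
- *Sphericity.* Standard corrections exist, so it is secondary.

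It is also fair to say that a right to withdraw points more to children leaving for good than to isolated missed visits. That favours the smaller loss figures.

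**Conclusion.** The concern holds in a limited form. For the label count in nutrient consumption, standard repeated-measures ANOVA without imputation would exclude every child lacking one of the three visits. That is hard to reconcile with the stated intention-to-treat analysis and discards usable data. With an assumed 10, 15 or 20% missing at each follow-up, the loss is 10, 15 or 20% if the same children miss both visits and 19, 28 or 36% if the absences are independent. The article does not say where the trial will fall, and the loss is nil if visits are complete or imputed. The arithmetic is certain; the missingness rates and patterns are assumptions.

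**What to change.** In Statistical Analysis, replace the repeated-measures ANOVA for the label count with the mixed-effects model already planned for food and beverage selection. Specify arm, visit, arm-by-visit interaction and a child random effect. Use all available observations, with each dyad analysed in the arm allocated to its school. Account for school as well, and say openly that four schools allow only a poorly estimated school effect.

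The cost is a change of wording for one outcome, with a method the team already intends to run; the article's Results section says recruitment has not begun. The small downside is reliance on a missing-at-random assumption: bias from loss that depends on unobserved outcomes is not removed. If the ANOVA is kept, the plan should state how children with a missed visit stay in the analysis.

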#### Food and Drink Selection

The percentage of products purchased by each participant in the online store, whose content indicates “high in calories, sugar, fat, and sodium” and the average content of these nutrients in 100 g of each product will be measured.

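### The planned analyses of change do not say that the outcome's own baseline value is conditioned on, which may cost precision that a fuller mixed model would recover

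*Protocol article*

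**What the plan says.** The Statistical Analysis section of the protocol article names two outcome analyses. For selection, a mixed-effects model is to estimate the intervention's effect "on changes in food and beverage selection, adjusting for confounding variables". For warning labels: "Repeated measures ANOVA will be used to evaluate the change in the number of warning labels in nutrient consumption between groups and throughout the intervention". Neither sentence defines change, and neither says how the baseline value of the outcome enters.

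In a separate paragraph, t tests and chi-square tests, with Mann-Whitney for nonnormal data, "will be used to compare baseline characteristics between the intervention and control groups".

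The baseline value is available. Time Frame puts the shopping task on the site, for caregiver and child together, and names the "online shop simulator at the 3 measurement points (baseline, 3 months, and 6 months"). The selection outcome is defined per participant under Food and Drink Selection: "The percentage of products purchased by each participant in the online store". Allocation is by school (Recruitment and Study Design): "Schools will be randomized into 2 groups: intervention and control". There are 4 schools in all.

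**The concern.** A change score gives the baseline a fixed coefficient of 1. A repeated measures analysis that treats baseline as one more response, with its own free mean in each arm, comes to the same thing when arms are compared on the difference from baseline. That is the usual form of the named ANOVA. If an outcome correlates only moderately with itself 3 to 6 months later, a coefficient of 1 is too large and adds noise. A single simulated shopping exercise or one 24-hour recall may well behave that way. With few schools, the arms are also likely to differ at baseline by chance, and an unadjusted change then carries regression to the mean into the effect estimate.

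The baseline tests add a smaller problem. They treat children as independent although schools were allocated, so school differences alone can produce small p-values.

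At stake is precision in a trial with 4 randomised units, where a better use of data already planned costs very little.

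**Working it through.** **Inputs.** From the article: 4 schools, outcomes measured at baseline and two follow-ups, effect expressed as change. The article shows no SD, ICC, cluster size or baseline-to-follow-up correlation, so there is no figure of its own to reproduce. All such values below are assumptions. Two schools per arm is also assumed, since the split is not stated.

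**Step 1: child level only.** Let r be a child's baseline-to-follow-up correlation, with equal variances. Relative to an analysis that ignores baseline (variance 1):

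- change: 2(1 − r)
- baseline-adjusted: 1 − r²
- ratio: 2(1 − r)/(1 − r²) = 2/(1 + r)

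Results:

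- r = 0.3: 1.40 against 0.91, ratio 1.54
- r = 0.5: 1.00 against 0.75, ratio 1.33
- r = 0.7: 0.60 against 0.51, ratio 1.18

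A generalised least squares check with three time points and compound symmetry gave the same values. Free baseline means per arm gave 1.40, 1.00 and 0.60; a common baseline mean gave 0.91, 0.75 and 0.51.

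**Step 2: add schools.** Assume total variance 1, ICC 0.05 (0.05 between schools, 0.95 within), 60 children per school and child-level r = 0.3. Let s be the correlation of the true school effects between baseline and follow-up.

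- Variance of a school mean at one time: V = 0.05 + 0.95/60 = 0.0658. This is also the result if baseline is ignored.
- Covariance of a school mean over time: C = 0.05s + 0.95 × 0.3/60 = 0.05s + 0.00475
- Change: 2(V − C)
- Child-level coefficient of 0.3 alone: 0.05(1 + 0.09 − 0.6s) + 0.95(1 − 0.09)/60
- Equal arm means at baseline with school and school-by-time effects: V − C²/V

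For s = 0.9, C = 0.04975:

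- change: 2(0.06583 − 0.04975) = 0.032
- child-level coefficient alone: 0.0275 + 0.0144 = 0.042
- constrained model: 0.06583 − 0.03760 = 0.028, a ratio to change of 0.88, or about 12% less

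For s = 0.5, C = 0.02975:

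- change: 2(0.06583 − 0.02975) = 0.072
- child-level coefficient alone: 0.0395 + 0.0144 = 0.054
- constrained model: 0.06583 − 0.01344 = 0.052, a ratio to change of 0.73, or about 27% less

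The arm difference is the same multiple of the school-mean variance in each case, so the ratios carry over. They treat the variance components as known.

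**Step 3: the baseline tests.** With 60 children per school the design effect is 1 + 59 × ICC: 1.59, 3.95 and 6.9 for ICC 0.01, 0.05 and 0.10. A nominal 5% test that ignores school then rejects with probability 2[1 − Φ(1.96/√design effect)], about 12%, 32% and 46%, through school variation alone.

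**The case against.** The strongest reply is that the article does not state an inefficient analysis. A mixed model for change could have the baseline as covariate, or a common baseline mean; both have the baseline-adjusted variance of step 1, so there would be no loss. This stands for the mixed-model sentence. It is weaker for the repeated measures ANOVA, whose usual form leaves the baseline means free in each arm.

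Second, the child-level gain of step 1 ignores the main variance component of a trial with 4 schools. This also stands. Where school differences persist (s = 0.9), adding only a child-level baseline coefficient is worse than a change score, 0.042 against 0.032. Nor can one say that change is worse than ignoring baseline whenever r is below 0.5: here r is 0.3, yet change gives 0.032 against 0.0658. But the same inputs favour the model that conditions on baseline at both levels in both cases, so the objection decides the form of the remedy and does not remove it.

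Third, a reader might infer that the baseline tests choose the confounders. No sentence says so, and the tests stand in a different paragraph from the model. A reader might also count the unnamed confounders as a fault. A condensed article may leave them to the full protocol or analysis plan, so they are not one.

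**Conclusion.** The point holds as a recommendation, not as a demonstrated error. The article frames its effect as change, names a method that usually leaves baseline free per arm, and does not mention conditioning on a baseline value it will have. A reader might conclude that the plan rejects baseline adjustment and certainly wastes precision; the text supports neither, because its mixed model is compatible with full adjustment.

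If the less efficient reading is meant, the child-level variance is inflated by a factor of 1.54 to 1.18 for r from 0.3 to 0.7. Counting schools, the recoverable part is about 12% at a school-level correlation of 0.9 and 27% at 0.5, on the assumed 60 children per school, ICC 0.05 and r = 0.3. Other inputs would give other figures. The small number of schools remains the larger limit on precision, and no handling of baseline removes it.

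**What to change.** State what change means and how baseline enters. Preferably, analyse the 3- and 6-month values in a longitudinal mixed model that includes baseline as a response, constrains the arm means to be equal there, and has school and school-by-time effects. Use the same form in place of the repeated measures ANOVA. The alternative is the child's own baseline value as covariate together with a school-level baseline term. A child-level baseline coefficient alone should not be relied on.

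Report baseline characteristics descriptively by arm and by school, and drop the t, chi-square and Mann-Whitney comparisons.

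The cost is wording and slightly more modelling work. No new data are needed, and the article says recruitment has not begun. The real downside is that 4 schools estimate variance components poorly. A school-level comparison of 2 against 2 has 2 degrees of freedom (critical value 4.30), and a baseline coefficient estimated from the 4 school means would leave 1 (12.71). This is a reason to prefer the constrained model over the alternative and to state the small-sample method in advance.

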### Ethical Considerations

The protocol has obtained ethics approval by the bioethics committees of the Hospital Infantil de México Federico Gómez (HIM/2022/054). This protocol has also been registered with ClinicalTrials.gov (NCT06102473).

The objectives and activities of the study will be explained to the caregivers and children. To participate, they must sign the informed consent and informed assent forms to give their authorization to participate, with confidentiality guaranteed.

The website will contain health education material and an online shop to simulate the selection and shopping of food and beverages. No personal or medical information will be uploaded to the website. The results will only be used for the study and will be stored by the research team on password-protected computers. In case of any changes to the protocol, the ethics committee will be informed.

## Results

The protocol was registered in 2022 and was approved by the committees of the Federico Gómez Children's Hospital of Mexico, and they also obtained federal resources for the project. We expect to begin the study in schools in September 2024. We are not recruiting yet. The results will be analyzed and published in April and May 2025.

## Discussion

### Expected Outcomes

This protocol aims to study a public health policy in Mexico, which seeks to contribute to improving the health of the Mexican population by facilitating the understanding of nutritional information about ultraprocessed foods and beverages using front-of-package warning labeling. Studying the effects of this intervention on the population is essential for continuing with the initiative, improving it, or considering other measures to achieve the expected health outcomes.

Some studies have been conducted around the world on different types of front labeling, exploring their effectiveness in selecting and purchasing healthier foods.

A study on adults [24] explored the effectiveness of different types of frontal labeling. Participants were given a brief educational session through a smartphone app before being exposed to 2 experimental shopping tasks. The study found that all types of front labeling, after the educational intervention, resulted in better food selection. In Mexico, a study [25] provided guidance on front labeling via video before participants engaged in online food selection, showing positive effects on food selection.

Another study [26] demonstrated that nutritional warning labels with stamps significantly reduced the percentage of participants who selected products with excessive content of at least one nutrient, compared to the control group (62% vs 85%), and a statistically significant difference was observed for participants who selected products with an excess of certain nutrients, such as sugar (*P*<.001), saturated fats (*P*<.001), and sodium (*P*=.01).

A study in the United States [27] targeting parents concluded that warning labels on sugary beverages reduced the purchase of these products for their children. Although the evidence indicates that front-of-package warning labels can improve the selection of foods and beverages, the effects of these labels on the pediatric population and how children influence the selection and purchase of foods in their homes are still unknown.

On the other hand, the guidance received by participants in the aforementioned studies is limited to ensuring understanding of reading the label.

One limitation of the study is that the exercise of food and beverage selection will be made in a simulated shopping scenario, which may differ from real-life situations of food and beverage purchasing and consumption; however, this study is important to determine whether a structured educational intervention on key nutrients and raising awareness about their implication in health enhances the effects of front-of-package warning labeling to reduce overweight and obesity as well as other chronic diseases, such as diabetes and hypertension.

